### Outcomes {12}

The primary outcome is change in parental solicitous/protective behaviors. Secondary outcomes include parent risk and protective factors and child health and symptom outcomes. Participant outcomes will be assessed at baseline, immediate post-intervention (6 weeks) and at 6-month, 12-month, and 18-month follow-up periods. See also Sects. 6a and 18a.

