### Sample size {14}

Based on our prior studies with the intervention [43], we expect the intervention effect sizes for our primary outcome measure in the range of 0.30–0.40 (Cohen’s *d*). Using Optimal Design software [44], we calculated that a sample size of 210–380 families is sufficient to detect the expected effect sizes with a power of 0.80 and alpha = 0.05. Power to detect mediation in analyses was calculated using Monte Carlo estimation methods. For single mediator models such as those proposed here, a sample size of 368 has > 0.80 power to detect a medium sized indirect effect that explains 13% of the variance in the outcome.

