***Outcome and process measures***							
Adult Responses to Children’s Symptoms (ARCS), Protectiveness subscale [51, 52] (primary outcome)	15-item Protectiveness subscale assesses parental protectiveness related to child illness behavior	P/C	X	X	X	X	X
Generalized Anxiety Disorder scale (GAD-2) [53]	2-item measure used for screening of parent anxiety disorder	P/C	X	X	X	X	X
PHQ-2 [54]	2-item measure used for screening of parent depression	P/C	X	X	X	X	X
PROMIS Pain Intensity Scale—Short Form [55]	3-item parent proxy and child self-report assessing child pain intensity in past 7 days	P/C, Ch	X	X	X	X	X
Pain Catastrophizing Scale (PCS)—Short Form [56, 57]	6-item measure that assesses parent catastrophizing thoughts or feelings accompanying the experience of pain	P/C	X	X	X	X	X
Positive and Negative Affect Schedule (PANAS) [58]	One 10-item scale measures parent positive affect and the other 10-item scale measures negative affect on a 5-point Likert scale	P/C	X	X	X	X	X
Multidimensional Scale of Perceived Social Support (MSPSS) [59]	12 items that measure the extent of social support received by parent from 3 sources: friends, family, and significant others. Types of social support assessed by the MSPSS include emotional, tangible, informational, social network support, and esteem	P/C	X	X	X	X	X
Children’s Somatic Symptoms Inventory (CSSI-8) [60]	8 items assess the severity of child’s nonspecific somatic symptoms. The set of GI symptoms (pain, nausea, upset stomach) are used to measure GI symptom severity	Ch	X	X	X	X	X
ROME IV Functional Abdominal Pain Questions [61]	5 items assessing ROME IV criteria for upper and lower child functional abdominal pain—frequency, severity, location, and association with eating (lower only)	P/C	X	X	X	X	X
Pediatric Quality of Life Inventory—Short Form (PedsQL-SF) [62, 63]	Brief measure of child health-related quality of life. The 15 items in the PedsQL comprise four Generic Core Scales: Physical Functioning (5 items), Emotional Functioning (4 items), Social Functioning (3 items), and School Functioning (3 items)	P/C, Ch	X	X	X	X	X
Client Service Receipt Inventory (CSRI) [64]	Validated, comprehensive inventory of health care services incurred due to the child’s symptoms that uses a standard response timeframe of the past 6 months. Parents report on three sources of child health care costs: direct medical service use, direct non-medical costs, and indirect costs	P/C	X		X	X	X

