#### Analyses by aims

Aim 1: Determine the efficacy of a preventive SLCBT intervention delivered to parents with IBS compared to a time and attention placebo/education condition (EC) at post-intervention, and at 6-, 12-, and 18-month follow-up periods. Analyses for this aim will use an intent-to-treat and dose–response approach. Intent-to-treat analyses will test associations between a dichotomous treatment assignment variable and primary (hypothesis 1) and secondary parent outcomes (hypothesis 2), as well as child health and symptom outcomes (hypothesis 3). Efficacy tests will be conducted using multilevel modeling (MLM) to maximize power and account for the longitudinal design with nesting of observations within person/family. In addition, the use of multilevel modeling allows estimation of intervention effects at a specific time point (intercept) and change over time in intervention effects (slope; time × intervention interaction). For example, to test hypothesis 1, we will estimate a series of MLMs testing the effect of the dichotomous intervention assignment variable on the level (intercept) of Adult Response to Children’s Symptoms (ARCS) scores at each time point by systematically re-centering the intercept (e.g., model 1: intercept at post treatment, model 2: intercept at 6 months, etc.). Next, we will test the association between intervention assignment and the slope of ARCS scores across time points (time × intervention interaction). Controls will include parent age and sex, as well as child sociodemographic characteristics and parent pre-treatment irritable bowel syndrome severity. Dose–response analyses also will use MLM as described above; however, the dichotomous treatment assignment variable will be replaced with a treatment engagement score (e.g., modules completed).

Aim 2: Determine the contribution of changes in parental risk and protective factors as mediating treatment effects. Hypothesis 4 states that changes in parental risk and protective factors will mediate treatment effects on child health-related quality of life. Following the procedures outlined by Muthen and colleagues [66], we will test whether and to what extent parent pain catastrophizing mediates the association between intervention group and parent solicitous responses to child symptoms. Similar models will test other mediators, as well as secondary parent and child outcomes.

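### The primary outcome has no designated time point or contrast: hypothesis 1 is tested at four time points and on a slope, unranked and unadjusted, while the trial is sized for one test at 0.05

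*Protocol article*

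**What the plan says.** All references are to the protocol article.

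- Outcomes {12}: "The primary outcome is change in parental solicitous/protective behaviors". No time point is attached, and the Abstract gives none either.
- Table 2: the instrument is the ARCS Protectiveness subscale ("15-item Protectiveness subscale assesses parental protectiveness related to child illness behavior"), collected at baseline and at all four later assessments.
- Analyses by aims, Aim 1: efficacy is to be determined "at post-intervention, and at 6-, 12-, and 18-month follow-up periods". For hypothesis 1, a series of multilevel models tests the effect of assignment on ARCS "scores at each time point by systematically re-centering the intercept (e.g., model 1: intercept at post treatment, model 2: intercept at 6 months, etc". After that, "we will test the association between intervention assignment and the slope of ARCS scores across time points (time × intervention interaction").
- Sample size {14}: 210 to 380 families "sufficient to detect the expected effect sizes with a power of 0.80 and alpha = 0.05", for d between 0.30 and 0.40. This is the only alpha in the article.
- Objectives {7}: hypothesis 1 is worded as a level claim, that REACH parents will show lower solicitous behaviour than control parents.

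**The concern.** The article is not silent about the primary test. It sets out five tests on the primary measure and gives none of them priority. The outcome definition, the sample size and the analysis therefore do not describe the same test.

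The five results can disagree. An early benefit that fades would give a difference at post-intervention, none at 18 months, and a slope favouring control. A benefit that stays constant after treatment could show in the levels with little slope. The article does not say which pattern would support hypothesis 1.

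Two things are at stake. If any one result may be called success, the error rate on the primary outcome is above 0.05. And the headline time point could be chosen after the results are seen; the statisticians are not blinded to assignment ({17a}, {17b}).

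**Working it through.** **1. The plan's own sample size.** Total N for two equal arms is 2 × ⌈2(z₁₋α/₂ + z₀.₈₀)²/d²⌉. The article does not state sidedness; I assume two-sided.

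- α = 0.05: 2(1.960 + 0.842)² = 15.70. For d = 0.30, 15.70/0.09 = 174.4, so 175 per arm and 350 in total. For d = 0.40, 15.70/0.16 = 98.1, so 99 per arm and 198 in total.
- α = 0.01 (Bonferroni over five): 2(2.576 + 0.842)² = 23.36. This gives 520 in total for d = 0.30 and 292 for d = 0.40.

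The stated 210 to 380 is not reproduced exactly; it is 6% to 9% above 198 to 350 (210/198 = 1.06, 380/350 = 1.09). The software inputs are not given, so I do not call this an error. The range fits a single test at 0.05, not a level split over five.

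**2. Chance of at least one false positive, if any of the tests at two-sided 0.05 counts.** The within-person correlation ρ is not in the article. I take 0.3 to 0.8, equal between all visits. Visits are placed at 0, 1.5, 7.5, 13.5 and 19.5 months, because the follow-ups count from the end of the intervention (mean 8.4, sum of squares 268.2).

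In a linear-time model fitted to all five visits, up to a common factor:

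- Cov(level at s, level at t) = ρ + (1 − ρ)[1/5 + (s − 8.4)(t − 8.4)/268.2]
- Var(slope) = (1 − ρ)/268.2
- Cov(level at t, slope) = (1 − ρ)(t − 8.4)/268.2

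With freely estimated means, the four post-baseline differences have pairwise correlation ρ, and the slope is their linear contrast. One million multivariate-normal draws give:

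| ρ | Linear, 4 levels | Linear, 4 levels + slope | Free, 4 levels | Free, 4 levels + slope |
|---|---|---|---|---|
| 0.3 | 0.10 | 0.13 | 0.17 | 0.20 |
| 0.5 | 0.09 | 0.13 | 0.16 | 0.19 |
| 0.7 | 0.08 | 0.12 | 0.13 | 0.17 |
| 0.8 | 0.07 | 0.12 | 0.11 | 0.15 |

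If the linear model is fitted to the post-baseline visits only, the four levels give 0.112 to 0.079 and all five tests 0.135 to 0.119. In any linear-time model only two parameters are tested, so the rate cannot exceed exp(−1.96²/2) = 0.147.

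**3. What the straight line does to a single-time contrast.** Suppose the true difference is 0 at baseline and a constant 0.30 SD at all four later visits.

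- Mean difference: 4 × 0.30/5 = 0.24.
- Fitted slope: 0.30 × 8.4/268.2 = 0.0094 per month.
- Fitted difference at post-intervention: 0.24 + 0.0094 × (1.5 − 8.4) = 0.175, not 0.30.
- Variance factor there: ρ + (1 − ρ)(0.2 + 6.9²/268.2) = ρ + 0.3775(1 − ρ), which is 0.564 at ρ = 0.3 and 0.876 at ρ = 0.8.
- Standard error at N = 460: √(4 × 0.564/460) = 0.070 and √(4 × 0.876/460) = 0.087.
- Power at two-sided 0.05: 0.71 (ρ = 0.3) down to 0.52 (ρ = 0.8).

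A plain comparison at one visit with d = 0.30 and N = 460, without dropout, has power 0.90.

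**The case against.** **The multiplicity rule may be in an analysis plan that is not shown.** That is fair, and the absence of an adjustment method is not the point here. Which contrast answers the primary question, however, belongs to the outcome definition and the sample size, and the article does fix the primary analysis, as a series of tests of equal standing.

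**The inflation is inferred.** A reader might conclude that each test is run at 0.05, that any success counts, and that the false-positive rate is therefore two to four times nominal. The article supports none of this as fact: Aim 1 gives no per-test level and no success rule. Re-centred intercepts with one slope term most naturally describe linear time, where the five-test figure is about 2.3 to 2.6 times 0.05 and at most 2.9 times. Four times needs freely estimated time points and a correlation near 0.3. This objection stands, and the size must be stated as conditional.

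**The slope may not be an equal fifth test.** Hypothesis 1 is about level, and the slope is tested afterwards. But {12} defines the outcome as change, so the article leaves this open. With the four levels alone in the linear model, the rate is 0.07 to 0.10.

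**Naming post-intervention as primary looks like the obvious repair, and one of wording only.** It is neither. Aim 1 lists all four time points and nothing in the article favours the first. Step 3 shows that the linear model can shrink that contrast and cost power.

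**Conclusion.** The point holds in this form: the primary outcome has no designated time point or contrast, and its hypothesis is tested in five unranked ways while the trial is sized for one. That part rests on the text alone.

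The size is conditional on any of the five results at two-sided 0.05 counting as success, and on assumed within-person correlations of 0.3 to 0.8. It is then about 0.12 to 0.13 for five tests in the linear-time model, 0.07 to 0.10 for the four levels alone, and up to about 0.20 with free time-point estimates. A flat statement that the error rate is two to four times 0.05 goes beyond the documents.

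**What to change.** Before outcome data are analysed, the investigators should name one primary contrast in {12} and {20a}, at two-sided 0.05. It could be the REACH minus EC difference in ARCS Protectiveness at one stated time point, or the average difference over the post-baseline time points. The choice is theirs. Time should enter the primary model as categorical, so that a straight line through baseline does not distort the contrast. The remaining time points are tested in a stated fixed order or reported as secondary, and the slope is secondary. {14} should say that its effect size refers to the named contrast.

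The cost is an amendment to the text and to the time term of the model. Designating one contrast keeps 0.05 for the primary test and needs no larger sample. Keeping all five tests with a Bonferroni split would need 520 families at d = 0.30, above the target of 460, where power would be 0.74 without dropout. The downside is that an effect seen only at a non-primary time point can no longer be claimed as confirmatory. Recruitment is expected to run until April 2027 (Trial status), so the choice can still be fixed before final data exist.

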### Trial design {8}

This study utilizes a RCT with parallel 1:1 assignment to two study arms, (1) REACH, a SLCBT prevention intervention, and (2) an educational comparison condition (EC). Figure 2 provides the study recruitment flow and condition allocation.

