### Assignment of interventions: allocation

#### Sequence generation {16a}

Group allocation will be determined using a computer-generated algorithm [45, 46] with equal assignments to each study arm, using randomly selected block sizes stratified by self-reported parent sex at birth.

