#### Concealment mechanism {16b}

Allocation concealment will be ensured, as randomization does not occur until after baseline measurements have been completed.

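### The planned contrasts on ARCS level do not adjust for baseline ARCS, which costs precision and lets part of any chance baseline difference into the estimates

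*Protocol article*

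**What the plan says.** Outcomes {12} defines the endpoint as a change: "The primary outcome is change in parental solicitous/protective behaviors". Table 2 names the instrument ("15-item Protectiveness subscale assesses parental protectiveness related to child illness behavior") and marks it for collection at T1 (baseline) and at T2 to T5.

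Under Concealment mechanism {16b}, "randomization does not occur until after baseline measurements have been completed". Trial design {8} gives "parallel 1:1 assignment to two study arms", and Sequence generation {16a} allocates "using randomly selected block sizes stratified by self-reported parent sex at birth". Parent sex is the only stratification factor, so the design does not balance baseline ARCS.

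Analyses by aims, Aim 1, sets out two steps for hypothesis 1. The first is a series of multilevel models of the arm effect "on the level (intercept) of Adult Response to Children’s Symptoms (ARCS) scores at each time point by systematically re-centering the intercept". The second is the time-by-arm interaction: "Next, we will test the association between intervention assignment and the slope of ARCS scores across time points". The covariates are then named: "Controls will include parent age and sex, as well as child sociodemographic characteristics and parent pre-treatment irritable bowel syndrome severity". The text does not say whether T1 ARCS is one of the repeated outcomes, and it states no constraint that the arms share a mean at T1.

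**The concern.** In a trial with a repeated questionnaire outcome, the baseline score of that same questionnaire is usually the most useful covariate. Here it is measured on every family before allocation, yet the named list takes a different pre-treatment score (IBS severity) and passes over ARCS.

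Two things are at stake for the level contrasts. First, if the arms differ by chance on ARCS at T1, part of that difference appears in the estimated effect at later visits. Second, variance that baseline could explain stays in the error term, although Aim 1 gives power as a reason for choosing multilevel modeling. The same applies to each secondary parent and child outcome measured at T1.

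**Working it through.** **Inputs from the protocol article.** d = 0.30 to 0.40, alpha 0.05, power 0.80 and 210 to 380 families (Sample size {14}); target 460 (Eligibility criteria {10}); 1:1 allocation.

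**Assumptions.** The test is two-sided. SD = 1. Data are complete. The correlation rho between baseline and follow-up ARCS is not given, so I use 0.3, 0.5 and 0.7. For the multi-wave check, visits are at 0, 1.5, 7.5, 13.5 and 19.5 months, with compound symmetry.

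**The plan's own figure.** Total N = 4(1.960 + 0.842)²/d², rounded up per arm, gives 198 at d = 0.40 and 350 at d = 0.30, against the stated 210 and 380. I do not reproduce the stated figures, but they are on the conservative side (power 0.826 and 0.832) and the software inputs are not shown. Nothing below depends on this.

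**Chance imbalance at N = 460.** The SE of the baseline arm difference is 2/√460 = 0.093 SD, so its 95% range is ±1.96 × 0.093 = ±0.18 SD. In an unadjusted single-time contrast about rho times that difference carries over. At the edge of the range this is:

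- rho 0.3: 0.05 SD
- rho 0.5: 0.09 SD
- rho 0.7: 0.13 SD

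The expected effect is 0.30 to 0.40 SD.

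**Precision of a single-time contrast.** Adjustment for baseline multiplies the variance by 1 − rho². Power is Φ(d/SE − 1.96) with SE = 0.0933 × √(1 − rho²). Unadjusted at d = 0.30: 0.30/0.0933 = 3.217, so power = Φ(1.257) = 0.896.

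| rho | variance factor | power, N = 460, d = 0.30 | N for 80% power, d = 0.30 |
|---|---|---|---|
| none (unadjusted) | 1.00 | 0.896 | 350 |
| 0.3 | 0.91 | 0.921 | 318 |
| 0.5 | 0.75 | 0.960 | 262 |
| 0.7 | 0.51 | 0.995 | 178 |

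**Does placing T1 among the outcomes solve it?**

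- With a free arm difference at every visit, the variance of a single-visit contrast is unchanged (factor 1.00).
- With a straight line through all five visits, the weight on the T1 arm difference in the contrast at 1.5 months is 1/5 + (1.5 − 8.4)(0 − 8.4)/268.2 = 0.416. Here 8.4 is the mean visit time and 268.2 the sum of squared deviations. Baseline imbalance therefore still enters. At 19.5 months the weight is −0.148.
- With the T1 arm means constrained equal and later visits free, the variance factor is 0.91, 0.75 and 0.51, as with the covariate.

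**Gain over a multi-wave model.** With the straight line through T1 to T5, the variance factor at post-treatment is 0.564, 0.689 and 0.813 for rho 0.3, 0.5 and 0.7. The same power formula gives 0.990, 0.972 and 0.946. A straight line through T2 to T5 with T1 as covariate has factors 0.70, 0.60 and 0.42 (the T1-out values 0.79, 0.85 and 0.91 less rho²), so power is 0.970, 0.986 and 0.999. The power gain at post-treatment is thus smaller than in the single-time comparison. At rho 0.3 there is none, because the straight-line assumption already supplies more precision than the covariate does.

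**The case against.** The strongest reply is that the covariate sentence says what the controls include, not that the list is complete, and that a full analysis plan, not shown here, may specify how baseline is handled. That is possible. But the article does not leave covariates open. It names them, names a pre-treatment score among them, and names the contrast. A statistician following it as written would fit a model without baseline ARCS as a covariate.

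A reader might infer that the planned tests do not address change at all. The article does not support that. The time-by-arm slope test follows the level tests, and it addresses change if T1 is in the outcome vector. The point is confined to the level contrasts.

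A reader might also infer bias, or that a baseline difference passes through in full. Neither follows. Randomization keeps the contrasts unbiased and the type I error valid, and a single-time contrast carries only about rho times the difference.

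Three objections to the size also stand. The correlation is assumed. The single-time comparison overstates the power gain over a model that uses all waves. And d comes from prior work whose adjustment cannot be seen; if that d was already baseline-adjusted, part of the gain is counted twice. Finally, 368 families is not the right base for the calculation, because Sample size {14} gives that number for mediation; the target is 460.

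**Conclusion.** The point holds for the level contrasts on ARCS: as written, they are not adjusted for the outcome's own baseline. This is avoidable loss of precision and robustness, not an error that invalidates the test. At 460 families with complete data, unadjusted single-time power at d = 0.30 is already about 0.90; adjustment takes it to between 0.92 and 0.995 for rho from 0.3 to 0.7. The carry-over from chance imbalance is at most about 0.05 to 0.13 SD at the edge of its 95% range. The direct weight of 0.42 at post-treatment applies only to a straight-line model with T1 in the outcome, under the assumed visit times and compound symmetry. The facts about the covariate list are certain; the size depends on a correlation that the article does not give.

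**What to change.** State one of two options for the primary model:

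- model the post-baseline ARCS scores with T1 ARCS Protectiveness and its interaction with time as covariates; or
- keep T1 in the outcome vector and constrain the arm means to be equal at T1.

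Apply the same rule to every secondary outcome with a T1 value, using that outcome's own baseline. Say explicitly whether T1 is one of the repeated outcomes, so that the meaning of the slope test is clear as well.

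The cost is a sentence or two of wording. No new data are needed, and Trial status estimates that recruitment will run to April 2027, so the change can be fixed before the final data are available.

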#### Intervention description {11a}

##### Education control (EC) condition

Participants assigned to the control group will receive access to a web program and complete three modules focused on child health and safety behaviors, including sports and water safety, home and fire safety, and technology safety. The EC condition is designed to be completed in a 4-week period and uses several interactive elements to increase engagement including brief questions to assess participant knowledge, question/answer components, and instructional videos. The control condition is designed to match the active intervention in time, attention, and expectancy, three major components of the placebo effect. In two previous studies, a safety focused control condition produced credible treatment expectancy effects [42, 43].

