##### Social learning and cognitive behavioral therapy (SLCBT) condition

Participants assigned to the SLCBT group will complete a 4-week web-based intervention. The website includes an introductory module, three skills-training modules (i.e., strategies to promote wellness behaviors, use adaptive cognitive coping, model wellness behaviors for their children, and determine when it is appropriate to take further action regarding potential illness in their child), and a brief maintenance and summary module. The web modules were designed to be visually attractive and interactive in order to engage participants through using brief questions to assess participant knowledge, interactive question/answer components, instructional videos, and storyboards that participants can click through. Screenshots can be seen in Fig. 3. Additionally, participants are provided a “Toolbox” in which informational handouts can be accessed, downloaded, and printed. The handouts provide a summary of the knowledge provided in each module. Participants in each group are instructed to log in to the website for 3–4 weeks, approximately 20–30 min per week. Research team members will regularly assess web program usage for all participants and will send reminders up to two times each week as needed to encourage regular usage and completion of all modules.

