#### Plans to promote participant retention and complete follow-up {18b}

Participants will receive automated assessment survey invitations and reminders. Research coordinators will send reminders if assessments are not complete, until the completion of the assessment period. We will use a database checklist to ensure that all study procedures are being followed (including consents) and that all surveys are being completed according to schedule. Study staff will review study participant data and monitor parent responses. Participants will also receive gift card incentives for completing baseline and follow-up assessments. All study questionnaires will be completed online so that participants may complete them at a time and place that is convenient for them.

We will continue to collect outcome data from all participants, irrespective of intervention discontinuation or deviation from protocol. However, we will construct a variable for the amount of treatment completed (number of web-based modules) and conduct sensitivity analyses to evaluate impact on intervention outcomes.

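### The Aim 1 dose-response model replaces randomized arm with modules completed: as written it counts EC and REACH modules as one dose and tests a self-selected variable, though only in a supportive analysis

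*Protocol article*

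**What the plan says.** All references are to the Protocol article.

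- **Statistical methods {20a}, Analyses by aims, Aim 1.** The efficacy aim has two named approaches: "Analyses for this aim will use an intent-to-treat and dose–response approach". The second keeps the first one's model: "Dose–response analyses also will use MLM as described above", except that "the dichotomous treatment assignment variable will be replaced with a treatment engagement score (e.g., modules completed".
- **Same paragraph, covariates.** "Controls will include parent age and sex, as well as child sociodemographic characteristics and parent pre-treatment irritable bowel syndrome severity".
- **Intervention description {11a}.** EC parents "complete three modules focused on child health and safety behaviors". For the REACH arm, "The website includes an introductory module, three skills-training modules", and a short closing module is listed after these. Staff check programme usage in both arms.
- **Table 2.** Engagement is logins, modules and assignments taken from the website, with no distinction by arm.
- **Statistical methods {20a}, General analytic procedures.** ITT is the main analysis throughout.
- **Retention {18b}.** The same kind of variable appears with a different status: "we will construct a variable for the amount of treatment completed (number of web-based modules) and conduct sensitivity analyses".

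**The concern.** Two separate things go wrong when engagement takes the place of arm.

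The first is what the score counts. Both arms have modules and the arm term is gone, so a parent who finishes three safety modules has the same dose as a parent who finishes three REACH modules. The section on choice of comparators {6b} says that EC exists to control for time, attention and online usage. This model makes online usage the exposure and discards the contrast that EC was built to provide.

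The second is who has a high score. Completing modules is a choice made after randomization. Parents who finish a web programme may also be parents whose responses to their child would have changed anyway. Parent age and sex, child sociodemographics and baseline IBS severity do not measure that propensity.

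At stake is how a significant dose-response result would be read. Because it sits under the efficacy aim, it could be offered as support for REACH beside a null ITT result, although a gradient can arise with no REACH effect.

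**Working it through.** **Inputs from the article.** 460 parents (Eligibility {10}); 1:1 allocation (Trial design {8}); alpha 0.05 and expected d of 0.30 to 0.40 (Sample size {14}); 3 EC modules; REACH modules 1 + 3 + 1 = 5, if the introduction and summary are counted. The article gives no figure for the dose-response analysis, so there is none to reproduce.

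**Step 1: the score without any self-selection.** Suppose every parent completes everything. Then dose = 3 + 2 × arm, and the score is a relabelled arm variable. With d = 0.30 the fitted slope is 0.30 / 2 = 0.15 SD per module, while the effect spread over the five REACH modules is 0.30 / 5 = 0.06. If dose is instead the share of one's own modules, it equals 1 for everyone and nothing can be estimated. Neither scoring gives a REACH dose-response.

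**Step 2: self-selection with no REACH effect.** The documents give neither completion rates nor the link between engagement and outcome, so both are assumed. Each parent has a standard normal propensity u, and modules completed are binomial with maximum 3 (EC) or 5 (REACH). The outcome is −r·u + √(1 − r²)·e, with e standard normal. One outcome time is regressed on the score, two-sided at 5%, with N = 460.

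- Completion model A: probability Φ(0.9 + 0.8u), mean Φ(0.9 / √1.64) = Φ(0.70) ≈ 0.76.
- Completion model B: logistic in u, centred at 0.75, mean about 0.72.

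Share of simulated trials that reject:

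| Analysis | r = 0 | 0.1 | 0.2 | 0.3 |
|---|---|---|---|---|
| ITT (A and B) | about 5% | about 5% | about 5% | about 5% |
| Pooled count, A | 5% | 22% | 69% | 96% |
| Pooled count, B | 6% | 20% | 61% | 92% |
| EC coded 0, A | 5% | 7% | 16% | 31% |
| EC coded 0, B | 5% | 8% | 14% | 27% |
| REACH arm only, B | 5% | 19% | 53% | 88% |
| Share of own modules, B | 5% | 28% | 76% | 98% |

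Of the four scorings, coding EC as 0 helps most, but the error rate still rises with r. Equalizing the scales by using shares does not help.

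**Step 3: a real REACH effect (model B, d = 0.30, effect linear in REACH modules).** The true slope is −0.30 / (5 × 0.72) = −0.083 SD per module. The pooled count estimates −0.101 at r = 0 and −0.180 at r = 0.2, and 0.180 / 0.083 ≈ 2.2 times the true value. With shares and r = 0, power is 0.18 against 0.89 for ITT.

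**The case against.** The strongest reply is that nothing confirmatory depends on this analysis. ITT is expressly the main analysis, Aim 1 assigns hypotheses 1 to 3 to ITT, and {18b} calls the modules-completed work a sensitivity analysis. That stands, and it limits the severity. A reader might infer from the Aim 1 wording that dose-response carries equal weight in the efficacy claim. The article names the two approaches together but does not weight them equally, and the general procedures rank ITT first.

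Second, the article does not say how EC parents are scored. Modules completed is given as an example, and coding EC as 0 or analysing only REACH parents could be set out in an analysis plan that is not shown. This stands in part. Pooling is the natural reading, because arm is replaced in an otherwise unchanged model and the score is not arm-specific, but it is not explicit. The same holds for 3 against 5, since the introduction and summary might not be counted. Neither reading removes the self-selection.

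Third, the rejection rates come from assumed completion and correlation values, one outcome time and no covariates, whereas the plan is a longitudinal model with covariates. That is correct. A reader might take 69% or 96% as this trial's error rate, but the documents supply no value of r, and at r = 0 there is no excess.

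Fourth, an instrumental-variable estimate answers a different question from a gradient. True, but the gradient as specified does not bear on efficacy, which is the aim it is listed under.

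**Conclusion.** The concern holds as a moderate point about a supportive analysis. The article states a specific model, and that model is unsuitable for the aim it is listed under: as written it merges two different programmes into one dose and replaces the randomized contrast with a self-selected variable. This is a flawed stated rule and not detail left to another document.

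The size depends on how strongly engagement goes with outcome. At N = 460 with no REACH effect, correlations of 0.1 to 0.3 move the pooled-count rejection rate from about 20% to above 90% under both completion models. With EC coded 0 the range is about 7% to 31%. These figures illustrate the mechanism and do not predict this trial's error rate. The documents do not support the stronger inference that the primary result, its type I error or the sample size is compromised: the ITT comparison stays near 5% throughout.

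The status of the analysis also needs one label, since {20a} places it under efficacy and {18b} under sensitivity.

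**What to change.** 1. In {20a}, Aim 1, do not replace arm with engagement. Estimate the effect of REACH exposure by an instrumental-variable or complier-average causal effect (CACE) analysis, with randomized arm as instrument and exposure defined as the proportion of REACH modules completed, set to 0 in EC. State whether the introduction and summary modules count.
2. If a within-arm gradient is wanted, fit arm plus arm × proportion of own modules completed, and label it exploratory, because self-selection remains.
3. Call the analysis a sensitivity analysis in both {20a} and {18b}.

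The cost is a wording change and a different model on data already being collected; recruitment is expected to run to April 2027, so it can be made before analysis. The interval widens: the IV estimate divides the ITT difference by mean REACH exposure, so at an assumed mean of 0.76 it is roughly 1 / 0.76 = 1.3 times as wide, on the scale of full completion. The estimate also assumes that assignment acts only through modules completed, which partial viewing or use of the downloadable handouts could breach, and that the effect is linear in the proportion completed. Both assumptions should be stated beside the result.
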